### Engagement of HTR men using gender-specific implementation strategies

Health promotion initiatives that fail to incorporate gender perspectives into their implementation plans are usually less effective and, at worst, can perpetuate gender stereotypes that are not conducive to positive wellbeing [1]. The underpinning vision of SFL is to normalise conversations about health and wellbeing in Sheds and encourage help seeking, a vision that potentially conflicts with traditional norms of masculinity that are often regarded as being characteristic of more HTR groups [1]. Central to this approach is the positioning of Shedders as key stakeholders alongside provider organisations, researchers and the IMSA. This acknowledges Shedders as active participants in the overall process - from programme design to implementation to evaluation and indeed to informing strategies more broadly to engage HTR men in health. This also means investing in relationships, establishing credibility and tailoring new programmes around the needs of individual Sheds [33]. The implementation of the 10-week SFL format and application of implementation frameworks (see implementation research design) to guide the engagement process, also facilitates acceptability and optimises recruitment, participation and engagement in SFL.

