**Effectiveness- Implementation**	Does participation in Sheds for Life improve health knowledge attitudes, outcomes and behaviours among participants?	Pragmatic controlled Trial Quantitative Questionnaires administered at baseline, 3, 6 & 12 months Qualitative Focus groups, ethnography, key informant interviews	Core outcome tools Self-reported Health Rating Seeking health information rating 7-item Short Warwick- Edinburgh Mental Wellbeing Scale (SWEMWBS) 5- point Likert Scales assessing; comfort having a conversation about mental health, understanding mental health and identifying practical supports 3-Item UCLA Loneliness Scale. Rated on a 3- point scale. Higher scores equal increased loneliness ONS 11-point Scales 0–10 Life satisfaction and life worth 8 point scales 0–7 physical activity and walking measure The 9-item self-efficacy for exercise scale (SEE) Close support, belonging, trust Alcohol, smoking & fruit & vegetable consumption Cooking frequency, cooking style and 12 measure scale measuring confidence constructs in relation to cooking Supplementary outcomes: Questions measuring changes in confidence and knowledge in relation to supplementary components developed in collaboration with provider organisations Qualitative tools Semi-structured topic guides	Quantitative Core outcomes Subjective Wellbeing Help-seeking Physical Activity Mental Wellbeing Diet & Cooking skills Social Capital Self-efficacy Quantitative Supplementary outcomes Diabetes Awareness, SafeTALK suicide prevention, Digital Literacy, Oral Health, Cancer awareness, CPR Qualitative outcomes Changes in attitudes and behaviours Acceptability Adoption Appropriateness

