#### Evaluating the effectiveness of SFL- data collection

Questionnaires are administered to participants by a research team member trained in data collection procedures to ensure standardised measurement and questionnaire administration. Questionnaires are administered one-to-one in the Sheds setting to account for potential literacy issues, prevent respondent burn-out, limit missing data and build rapport and trust between the researchers and Shedders. To also minimise missing data, participants will be contacted by the IMSA in the days before the research team visit the Sheds to perform data collection. Due to the informal nature of the Sheds, absence of data for a participant does will not necessarily indicate dropout from SFL. During 6 and 12 month follow-up in Phase 1, Cohort 2 were experiencing COVID-19 restrictions and therefore questionnaires were administered via phone in order to promote participant retention and complete follow-up. The questionnaire was designed via a consultation process with stakeholders involved in the design and delivery of SFL with a view to optimising acceptability for SFL participants and also SFL providers who were interested in evaluating their individual components of SFL. Participant demographics are recorded at baseline and include date of birth, living arrangements, educational attainment, employment status relationship and ethnicity. Participants are also asked how long they had been a Shed member and how often they attend the Shed. Core health and wellbeing outcomes measured at all-time points up to 12 months consist of; subjective wellbeing, help-seeking, physical activity, mental wellbeing, diet and cooking skills, social capital and self-efficacy. Participants are also asked how often they seek information about their health.

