Self-rated health is measured using a single question Likert scale with high reliability among older men [49]. The single-item PA measure is used to record PA levels [50]. The Self-Efficacy for Exercise Scale (SEE) is used to measure physical activity self-efficacy [51]. Life worth and satisfaction are recorded using the Office of National Statistics subjective wellbeing 11-point scales [52]. Mental wellbeing is measured using the Short Warwick-Edinburgh Mental Wellbeing Scale (SWEMWBS) with raw to metric score conversion where a change of 2+ is considered relevant [53]. Loneliness is measured at all-time points using the UCLA 3-item scale measuring three dimensions of loneliness; relational connectedness, social connectedness and self-perceived isolation, with participants also asked at baseline to retrospectively rate their loneliness prior to joining the shed [54]. Social Capital is measured based on relevant recommendations from WhatWorksWellbeing [55], capturing trust, belonging and close support. Interpersonal trust is measured using the Office of National Statistics 11-point scale [52]. Lifestyle behaviours are also recorded - smoking (number smoked per day) and alcohol consumption (days drinking and units consumed per drinking session). Assessments of cooking and healthy eating behaviours are developed in conjunction with the partner organisation delivering the Healthy Food Made Easy component of SFL. Participants are asked about their levels of daily fruit and vegetable consumption, cooking style, cooking frequency and willingness to cook. Confidence constructs around cooking and healthy eating are measured via a 12 item Likert scale ranging from “not at all confident” to “very confident”. The questions were adapted from a protocol for community-based cooking interventions which were developed at a lower literacy level with varying levels of literacy among participants in mind [56]. The constructs used to assess cooking and healthy eating were previously validated [57] (See Table 2 for effectiveness outcome measures including optional components).

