#### Evaluating the effectiveness of SFL- data analysis

Questionnaire data is analysed using Statistical Packages for the Social Sciences (SPSS V 24). Descriptive statistics for each variable are calculated to inform participant characteristics. Intervention effect on health and wellbeing outcomes are determined by comparing the change scores from baseline to 3, 6 and 12 months, comparing data using inferential tests to identify significant differences set at *p* = 0.05. Analysis of subgroups based on criteria such as; Shed size location and timing of the intervention, will also be performed to identify significant differences in intervention effect between groups. Outcome data obtained from all participants are included in the data analysis, regardless of adherence to SFL. The intervention effects will be assessed at 3, 6 and 12 months based on those who completed follow-up at these time points. Assuming a worst case scenario for absentees i.e. that absentees failed to achieve a significant improvement in core health outcomes (physical activity, diet, mental wellbeing, subjective wellbeing, social capital and help-seeking), these worst- case scenario analyses will reflect the intention to treat principle. The numbers who achieved significant improvement at 3, 6 and 12 months will be presented as a percentage of those who were tested at these follow-up points. For the initial intervention effect worst-case scenario, the numbers who achieved significant improvements at 3 months will be presented as a percentage of those who were tested at baseline. The worst-case scenario for maintenance of this initial intervention effect will present the numbers who achieved significant improvements at 6 and 12 months as a percentage of those who were tested at the 3 month follow-up. Observed success rates will be compared between the intervention and comparison group in waiting using Chi-Square analysis.

A hybrid analytic approach of inductive and deductive analysis is applied to the participant transcripts. This means that whilst implementation frameworks are applied to inform implementation outcomes, the analysis process will remain open to findings that may emerge outside of those pre-set domains to allow assessment of intervention effect. In these circumstances, inter-rater reliability is used to cross-check coding strategies and interpretations are negotiated to agree on a ‘master’ code list.

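### Self-efficacy is a core outcome in two places but is left out, without a reason, of the list given the worst-case (absentee-as-failure) analysis

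*Protocol article*

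**What the plan says.** The protocol article names its core outcomes in three places.

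- **Table 2** (section *Effectiveness- implementation evaluation design*) gives "Quantitative Core outcomes Subjective Wellbeing Help-seeking Physical Activity Mental Wellbeing Diet & Cooking skills Social Capital Self-efficacy". Its core tools include "The 9-item self-efficacy for exercise scale (SEE").
- **The data collection section of Part 1** gives the core outcomes measured at every time point as "subjective wellbeing, help-seeking, physical activity, mental wellbeing, diet and cooking skills, social capital and self-efficacy". It adds that "The Self-Efficacy for Exercise Scale (SEE) is used to measure physical activity self-efficacy".
- **The data analysis section of Part 1** says that intervention effects are assessed in men who completed each follow-up. It then adds a worst-case analysis, meant to reflect intention to treat, in which absentees are assumed not to have improved. The outcomes covered are "core health outcomes (physical activity, diet, mental wellbeing, subjective wellbeing, social capital and help-seeking").

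On help-seeking, the engagement section states the programme's vision as to "normalise conversations about health and wellbeing in Sheds and encourage help seeking". Table 2 places "Seeking health information rating" among the core tools, together with 5-point items on comfort in talking about mental health, understanding it and identifying supports. The data collection section says, after its core list, that "Participants are also asked how often they seek information about their health".

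**The concern.** The worst-case analysis is the article's only stated safeguard against judging the programme on the men who turned up. A core outcome left outside it gets only the completer analysis, which cannot give a lower success rate and gives a higher one whenever anyone is absent and anyone improves. The article fixes this list itself and contradicts its own two earlier lists, so this is not detail merely left to another document.

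Two things are at stake. Results for self-efficacy would not be comparable with worst-case results for the other core outcomes. And a reader could not tell whether the omission was planned or a slip.

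A smaller concern is what a help-seeking result would mean. The nearest listed items record information-seeking, comfort, understanding and identifying supports. None records contact with a doctor or support service.

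**Working it through.** **Step 1: set the lists side by side.**

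| Domain | Table 2 | Data collection | Worst-case list (data analysis) |
|---|---|---|---|
| Subjective wellbeing | yes | yes | yes |
| Help-seeking | yes | yes | yes |
| Physical activity | yes | yes | yes |
| Mental wellbeing | yes | yes | yes |
| Diet and cooking skills | yes | yes | diet only |
| Social capital | yes | yes | yes |
| Self-efficacy | yes | yes | **absent** |
| Count | 7 | 7 | 6 |

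The first two lists agree fully. The third drops one domain and shortens the name of another. It adds none.

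**Step 2: the gap between the two analyses at 3 months.** The article gives no expected success rate, so there is no figure of its own to reproduce. Its definitions give:

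- completer rate s = (men improved at 3 months) / (men tested at 3 months)
- worst-case rate = (men improved at 3 months) / (men tested at baseline) = (1 − d) × s, where d is the share of men tested at baseline who are absent at 3 months
- gap = s − (1 − d) × s = d × s

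Inputs: d = 0.20 is the dropout allowance in *Participants and sampling*. That section does not tie it to a visit, so using it at 3 months is an assumption. The values of s are also assumptions, shown as a range.

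| Assumed s | Worst-case rate (0.80 × s) | Gap (0.20 × s) |
|---|---|---|
| 30% | 24% | 6 points |
| 50% | 40% | 10 points |
| 70% | 56% | 14 points |

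**Step 3: later visits.** At 6 and 12 months the worst-case denominator is the men tested at 3 months, so the table above does not carry over. The gap then depends on how many men were tested at the later visit relative to 3 months, which the article does not give.

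**Step 4: help-seeking.** It appears in all three lists, so the lists do not conflict on it. Table 2 puts possible indicators of it under the core tools. What remains is the content of those items, described above.

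**The case against.** The best defence of the omission is that the worst-case list is headed as core *health* outcomes. Exercise self-efficacy might be thought not to be a health outcome, or the SEE might be counted under physical activity. The article says neither. Its data collection section puts self-efficacy among the core health and wellbeing outcomes and lists it separately from physical activity. The worst-case list also keeps social capital and help-seeking, which are no more narrowly health outcomes than self-efficacy. The objection shows that a reason could exist, but none is stated.

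It is also fair to say that *diet* may be shorthand. The article describes cooking and healthy eating as one block of assessments, so a reader might infer that cooking skills were excluded, but the text does not establish that. A clarifying word is enough.

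On help-seeking, a reader might infer that no tool measures it at all. The documents do not support that: the information-seeking rating and the items on conversation and supports are plausible indicators listed among the core tools. Which of them scores the domain is detail that a condensed article may leave to documents not shown. Nor can one say which men would be wrongly classed as improved or not improved, because no scoring rule is stated.

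Finally, attender-based percentages are to be reported as well, so like-for-like comparison across domains remains possible on that basis. That softens the problem but does not give self-efficacy a worst-case result.

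**Conclusion.** The inconsistency is real and specific. Self-efficacy is core in two lists, has a named instrument, and is missing without explanation from the one list that decides which outcomes get the worst-case analysis. As written, it would be reported only in men who attended follow-up.

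The size is 0.20 times the completer success rate at 3 months: 6, 10 or 14 points at assumed rates of 30%, 50% or 70%. This rests on 20% of men tested at baseline being absent at that visit. A reader might take 10 points as a ceiling. It is not, because the gap grows with both the success rate and the share absent.

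Physical activity, on which the sample size rests, is unaffected. Nothing in the article shows that the omission was made to favour self-efficacy. The help-seeking point is secondary and concerns how results are labelled.

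**What to change.** 1. In the data analysis section, replace the six-outcome list with the seven core outcomes of Table 2 and the data collection section, so that self-efficacy (SEE) follows the same absentee rule. If the exclusion is intended, give the reason.
2. State there that diet includes cooking skills.
3. Label Phase 1 help-seeking results by what the items record: information-seeking, comfort in talking about mental health, understanding it, and identifying supports.
4. Optionally, for Phase 2, whose recruitment the article schedules for September to December 2021, add one question on contact with a health or support service. Keep the existing items so that Phases 1 and 2 stay comparable.

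Items 1 to 3 are changes of wording and need no new data. The price is a less favourable worst-case figure for self-efficacy reported beside its completer figure. Item 4 costs one extra question per interview.

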Sheds are a community-based, grassroots movement which originated in Australia and have since grown exponentially in Ireland. Sheds have long been recognised not just as a suitable setting in which to actively promote and engage men in health but also as being imbued with inherent and organic health promoting qualities [26]. Sheds are autonomous grass roots spaces which are non-structured and informal, varying in size and resources. Sheds offer a safe and familiar environment for Shed members (‘Shedders’) and foster a sense of social support, belonging and camaraderie, through developing new skills, shared projects, activities, goals and decision making [27]. All of these factors have been linked with enhancing the health and wellbeing of the men who attend with social support, in particular, being frequently reported as a key enabler of men’s help-seeking [28]. The enhanced sense of belongingness that is attributed to the non-conventional setting of Sheds increases their appeal to typically HTR men [29–31]. This is also the case in more recent research which suggests that the Sheds have a protective effect against loneliness [32]. The inherent health promoting qualities of Sheds therefore present a strong foundation upon which to build structured health promotion programmes. Moreover, drawing from a rich source of past interventions that utilised strengths-based and gender-specific approaches, the Men’s Sheds setting is well-positioned to deliver tailored, targeted health promotion initiatives to what has been traditionally regarded as an inaccessible of HTR cohort of men [33]. Nevertheless, it is also critically important that such endeavours enrich rather than erode the ethos of the Shed environment, which means that programmes need to be pragmatically evaluated with Shedders at the centre of decision making [33, 34]. Conventional wisdom dictates that health interventions need to be delivered systematically, to be context free, with strict inclusion criteria. However, Sheds are not just highly variable, autonomous, non-structured spaces; these are the very characteristics that define the essence of Sheds and which need to be respected in order to uphold the integrity and ethos of the Sheds. The challenge therefore is to develop a pragmatic delivery design that can operate within an organic, non-structured space, where contextual factors vary, where attendance can be sporadic, and where there is no compulsion on members to undertake any activity.

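### On bounded scales, men already at the best score at baseline cannot count as successes, so the unadjusted chi-square of SFL against wait-list success rates partly reflects how many such men each group contains

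*Protocol article*

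**What the plan says.** The protocol article, under *Evaluating the effectiveness of SFL- data analysis*, describes two kinds of effect analysis. The first compares change scores from baseline to 3, 6 and 12 months, "comparing data using inferential tests to identify significant differences set at *p* = 0.05". The second turns each outcome into a success rate: "The numbers who achieved significant improvement at 3, 6 and 12 months will be presented as a percentage of those who were tested" at that follow-up.

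Two worst-case versions change only the denominator. For the initial effect, "the numbers who achieved significant improvements at 3 months will be presented as a percentage of those who were tested at baseline". For maintenance, the section presents "the numbers who achieved significant improvements at 6 and 12 months as a percentage of those who were tested at the 3 month follow-up".

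The group comparison is then fixed: "Observed success rates will be compared between the intervention and comparison group in waiting using Chi-Square analysis". No denominator is limited to men who could improve, and no adjustment for or stratification by baseline score goes with the chi-square. The planned subgroup analyses concern Shed size, location and timing, not baseline score.

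Table 2 lists 8-point scales running from 0 to 7 for the "physical activity and walking measure", and 0 to 10 scales for life satisfaction and life worth. *Participants and sampling* makes physical activity the primary outcome and admits all adult men in the Sheds who have adequate English and can consent, with no upper limit on baseline activity or wellbeing. It gives 212 men in 12 clusters for the first SFL cohort and 89 men in 3 clusters for the wait-list comparator. *Limitations* confirms that participants are not randomised.

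**The concern.** A success rate of this kind combines two things: how often men with room to improve do improve, and how many men have room. Only the first says anything about the programme. A man who scores 7 on physical activity before SFL starts, and still scores 7 at 3 months, falls in the same non-success category as a man who stays at 0.

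Randomisation would make the share of men at the best score similar in the two groups on average. Here nothing does. The cohorts come from different counties, Sheds volunteered and were purposively chosen for variety, and the comparator is only three Sheds, so one atypical Shed could shift its baseline distribution noticeably. If the shares differ, the chi-square can show a difference in the absence of any effect, or hide a real one. The chi-square is the only test that the article names specifically for SFL against wait-list.

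**Working it through.** **The plan's own figure.** The article gives no figure for ceiling shares or success rates. Its one computed quantity, the sample size, reproduces (106 × 2.4 = 254.4, rounded up to 255; 255 × 1.2 = 306) and has no bearing on this point.

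**Inputs from the article.** Numerator: men who improved. Denominator: all men tested. Test: chi-square at 0.05 (taken as two-sided, which is not stated). Group sizes: 212 and 89. Scale bounds: 0 to 7 and 0 to 10.

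**Assumed inputs.** *s* is the probability of success among men with room to improve. *c* is the share of men at the best baseline score. Neither is in the article, so ranges are shown.

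**Formula.** Men at the bound contribute no successes whatever threshold defines improvement, so

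observed rate = *s* × (1 − *c*).

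**No true effect (same *s* in both groups).** With *s* = 0.40 and ceilings of 20% (SFL) v 40% (wait-list): 0.40 × 0.80 = 0.32 against 0.40 × 0.60 = 0.24, an 8-point gap due to baseline alone.

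The chance that the chi-square rejects was computed as the equivalent pooled two-proportion test. For *s* = 0.5 and ceilings of 10% v 30%:
- Rates: 0.45 and 0.35. Pooled rate: (212 × 0.45 + 89 × 0.35) / 301 = 0.420.
- Null standard error: √[0.420 × 0.580 × (1/212 + 1/89)] = 0.0623. Critical difference: 1.96 × 0.0623 = 0.122.
- Standard error at the actual rates: √(0.45 × 0.55/212 + 0.35 × 0.65/89) = 0.0610.
- (0.122 − 0.10) / 0.0610 = 0.36, so the test rejects in about 36% of trials.

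The same calculation over the range:

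| Ceiling, SFL v wait-list | *s* = 0.3 | *s* = 0.5 | *s* = 0.7 |
|---|---|---|---|
| 20% v 20% | 0 points, 5% reject | 0 points, 5% | 0 points, 5% |
| 10% v 20% | +3, 8.0% | +5, 12.4% | +7, 20.8% |
| 10% v 30% | +6, 18.5% | +10, 35.8% | +14, 61.4% |
| 30% v 10% | −6, 21.3% | −10, 37.3% | −14, 60.5% |

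These rejection rates assume that all 212 and 89 men are followed up, and they ignore clustering. Clustering would change the rejection rates but not the differences in points.

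**True effect present.**
- 50% v 35% among men with room, ceilings 30% v 0%: 0.50 × 0.70 = 0.35 against 0.35 × 1.00 = 0.35. The effect disappears.
- 50% v 30% among men with room, ceilings 40% v 20%: 0.50 × 0.60 = 0.30 against 0.30 × 0.80 = 0.24. A 20-point effect appears as 6 points.

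**Effect of restricting the denominator.** In the 50% v 35% case, limiting the comparison to men with room (212 × 0.70 ≈ 148 against 89) restores 50% v 35%, with power of about 62% before clustering.

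**The case against.** Several objections have force.

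*Success is not defined for the individual man.* The article is a condensed account, and a fuller document may define the responder rule. That stands as far as the threshold goes. It does not remove the problem, because no definition of improvement lets a man at the bound improve. Only a rule that counts staying at the best score as success would do so, and the article's wording does not say that.

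*The chi-square is not the only effect analysis.* Correct. Change scores come first in the section. A reader might infer that the whole SFL against wait-list evaluation is compromised, but the text does not support that. Mean change is also limited by a scale bound, but the point here concerns success rates.

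*No ceiling imbalance is shown.* Also correct. A reader might infer a bias in favour of SFL, but the article gives no baseline distributions. The imbalance could run either way or be absent, and with equal shares there is no false difference.

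*Loneliness and SWEMWBS are weak examples.* The background section says that recent research "suggests that the Sheds have a protective effect against loneliness", which might suggest that many men start at the best loneliness score. Both groups are Shed members, so this gives no reason to expect a difference between them, and loneliness is not named in the data analysis section's list of core outcomes. For SWEMWBS the article says "where a change of 2+ is considered relevant" but does not make this the success criterion. If it were, men less than 2 points below the maximum would also be unable to succeed.

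*The lower all-men rate is not an error.* Agreed. With a common 30% ceiling, 50% v 30% among men with room becomes 35% v 21%, so 20 points become 14. That answers a question about all men tested, which is a legitimate quantity and fits the plan's inclusion of everyone's data.

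*The article already concedes non-randomisation.* It does, but the concession does not alter the unadjusted test.

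**Conclusion.** The point holds for the success-rate comparison on bounded outcomes, physical activity above all. The stated numerator, denominator and unadjusted test make the contrast depend on the share of men at the best baseline score, and a non-randomised comparison of 12 clusters with 3 gives no assurance that this share is equal. Under the assumed ceiling differences of 10 to 20 percentage points shown in the table, the spurious gap is 3 to 14 points in either direction, and a real effect can be reduced or cancelled. The actual size and direction are unknown. The finding does not show that the trial's results are biased, and it does not extend to the change-score comparison. It is a moderate weakness in one stated analysis that can be reduced cheaply with data already collected.

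**What to change.** Amend the data analysis section for each bounded outcome as follows.

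1. Keep the percentage of all tested men who improved, as a descriptive figure.
2. Report, for SFL and wait-list separately, how many men were at the best score at baseline, and how many of them stayed there or declined.
3. Base the SFL against wait-list success comparison on men whose baseline score leaves room for the required improvement (for physical activity, a baseline below 7 if any upward step counts). Adjust for baseline score or stratify by it. Restriction alone is not enough, because a man at 6 has one step available and a man at 0 has seven.
4. State the required improvement for each outcome, so that having room is defined from baseline data alone.

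Because the restriction uses only pre-intervention scores, it introduces no selection on anything that happens after SFL begins. The cost is some analysis wording, one extra table row per outcome and a smaller denominator, hence some loss of precision. Other baseline confounding between the cohorts remains and should still be acknowledged.

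### The 6- and 12-month worst-case rates divide by men tested at 3 months, so men absent at 3 months are dropped instead of counted as failures, contrary to the stated intention-to-treat principle

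*Protocol article*

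**What the plan says.** The rules are in the protocol article, Part 1, in the section on data analysis for effectiveness.

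- **Absentee rule:** "Assuming a worst case scenario for absentees i.e. that absentees failed to achieve a significant improvement in core health outcomes".
- **Principle claimed:** "these worst- case scenario analyses will reflect the intention to treat principle".
- **Observed rates:** the numbers improved at each follow-up "will be presented as a percentage of those who were tested at these follow-up points".
- **Worst case at 3 months:** "the numbers who achieved significant improvements at 3 months will be presented as a percentage of those who were tested at baseline".
- **Worst case at 6 and 12 months:** introduced as "The worst-case scenario for maintenance of this initial intervention effect", this presents "the numbers who achieved significant improvements at 6 and 12 months as a percentage of those who were tested at the 3 month follow-up".
- **Between-group test of success:** "Observed success rates will be compared between the intervention and comparison group in waiting using Chi-Square analysis".

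The data collection section of Part 1 adds that "absence of data for a participant does will not necessarily indicate dropout from SFL".

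**The concern.** The absentee rule and the intention-to-treat statement cover the worst-case analyses as a set. The 3-month rate follows them: every man tested at baseline is in the denominator, and an absent man counts as not improved. The 6- and 12-month rates do not. A man tested at baseline and absent at 3 months is left out of the denominator, so he is not counted as a failure.

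Two further problems follow from the same sentence. The numerator is not expressly limited to men tested at 3 months. Since absence at a visit is not dropout, a man missed at 3 months and seen at 12 months could enter the numerator without being in the denominator. Also, the rate is offered as a measure of maintenance, but a man who had not improved at 3 months and improved later would count as a success.

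These percentages would be read as a conservative floor for long-term benefit. Outcomes to 12 months are part of the stated aim, and the Dissemination section says that findings go into reports for participants, providers and policy makers. The error runs in the programme's favour.

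**Working it through.** **Plan's own figures.** The protocol gives no success rate and no 3-month attendance, so no stated result of this rule can be reproduced. The only attrition figure is the 20% dropout allowance under Participants and sampling: 106 × 2.4 = 254.4, rounded up to 255, and 255 × 1.20 = 306, as stated. That allowance carries no time point.

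**Inputs**
- n0 = men tested at baseline. For illustration, 212, the size of the first cohort (Participants and sampling).
- a3 = share of baseline men absent at 3 months. Assumed, 10% to 40%.
- n3 = n0 × (1 − a3), men tested at 3 months.
- x = men improved at 12 months. Assumed.

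**Step 1: same numerator, two denominators.** The planned rate is x/n3 and the baseline-denominator rate is x/n0. Their ratio is n0/n3 = 1/(1 − a3).

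| Assumed absence at 3 months | Ratio |
|---|---|
| 10% | 1/0.9 = 1.11 |
| 20% | 1/0.8 = 1.25 |
| 30% | 1/0.7 = 1.43 |
| 40% | 1/0.6 = 1.67 |

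**Step 2: worked example without returners.** Assume 20% absent at 3 months, so 212 × 0.8 = 169.6, about 170 tested. Of these, assume 144 are tested at 12 months and 72 have improved.
- Observed rate: 72/144 = 50.0%
- Planned worst case: 72/170 = 42.4%
- Baseline denominator: 72/212 = 34.0%

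The planned rate is below the observed rate but well above the rate obtained when every absentee counts as a failure.

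**Step 3: worked example with returners.** Assume 170 tested at 3 months and 185 at 12 months, because some men missed at 3 months are reached later, with 92 improved.
- Observed rate: 92/185 = 49.7%
- Planned worst case: 92/170 = 54.1%
- Baseline denominator: 92/212 = 43.4%

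If the numerator is not restricted, the worst case can exceed the observed rate.

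**Step 4: if the numerator is restricted to men tested at 3 months.** Let x be the improved men among those tested at 3 months and r the improved men among those absent then. The planned rate is x/n3 and the baseline rate is (x + r)/n0. The ratio is [1/(1 − a3)] × x/(x + r), so the Step 1 figures become an upper bound. The planned rate is still the higher one whenever x/n3 is greater than r/(n0 − n3), that is, whenever men absent at 3 months do worse later than men tested at 3 months, with those not seen counted as failures.

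**Step 5: maintenance.** Maintenance of an initial effect concerns men who had that effect. The planned denominator is all men tested at 3 months, improved or not, and the numerator is all men improved at the later visit, whatever their 3-month status. Neither part is conditional on improvement at 3 months.

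**The case against.** The strongest defence is that the denominator is disclosed and deliberate. The section separates a worst case for the initial effect (baseline denominator) from one for maintenance (3-month denominator), and a rate conditional on the 3-month assessment is a legitimate description. That stands as far as it goes, but it does not support the intention-to-treat label, which the section attaches to the worst-case analyses together. Nor does it make the rate one of maintenance, for the reason in Step 5.

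The defence can also say that a percentage of those tested at 3 months implies a numerator drawn from the same men. That reading is possible. It removes the mismatch in Step 3 and turns the ratios into upper bounds. The mismatch is therefore an ambiguity to close, not a demonstrated error; the loss of 3-month absentees from the denominator remains on either reading.

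It is also fair that these rates are secondary. The section determines the intervention effect from change scores, and no stated test, sample size or decision rule uses the 6- and 12-month worst-case percentages.

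A reader might go further and infer that absentees are counted as failures in both arms and the imputed rates then compared, which would favour SFL if the waiting group had more absentees. The document does not support this: the absentee rule names no arm, and the only between-group test of success named uses observed rates. For a single-group rate over all baseline men, counting absentees as failures does give the lowest possible value, so the 3-month worst case is sound. A reader might also take the 20% dropout allowance as planned loss by 3 months; the protocol does not say when that loss occurs.

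**Conclusion.** The point holds for the 6- and 12-month worst-case rates. As written, they contradict the section's own absentee rule, its intention-to-treat statement and its 3-month denominator. With the same numerator, they exceed the baseline-denominator rates by a factor of 1.11 to 1.67 for 10% to 40% absence at 3 months. The factor is 1.25 if the whole 20% allowance is assumed to fall by 3 months. The absence range is an assumption, and the factors are upper bounds if the numerator is confined to men tested at 3 months. The counts in the worked examples are illustrative, apart from the 212 in the first cohort.

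The point does not extend to the 3-month worst-case rate or to the between-group comparison, and it gives no ground for replacing the main analysis. Severity is moderate: the rates are descriptive, but they are labelled as a safeguard and would overstate long-term success.

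**What to change.** 1. For the worst-case rates at 3, 6 and 12 months, use all men tested at baseline as the denominator, with men absent at the visit in question counted as not improved. The numerator is then all men improved at that visit, including those missed at 3 months and seen later.
2. Report maintenance separately: men improved at 3 months who remain improved at 6 or 12 months, over all men improved at 3 months, with absentees counted as not maintained.
3. If a rate with the 3-month denominator is kept, describe it as conditional on being tested at 3 months, limit its numerator to those men, and drop the worst-case and intention-to-treat labels from it.

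This changes the analysis wording only and needs no new data. The downside is that the reported long-term percentages will be lower.
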